## Abstract

**Introduction:**

For non-ST-segment elevation acute coronary syndrome (NSTEACS) there is a gap between the use of class I guideline recommended therapies and clinical practice. The Global Registry of Acute Coronary Events (GRACE) risk score is recommended in international guidelines for the risk stratification of NSTEACS, but its impact on adherence to guideline-indicated treatments and reducing adverse clinical outcomes is unknown. The objective of the UK GRACE Risk Score Intervention Study (UKGRIS) trial is to assess the effectiveness of the GRACE risk score tool and associated treatment recommendations on the use of guideline-indicated care and clinical outcomes.

**Methods and analysis:**

The UKGRIS, a parallel-group cluster randomised registry-based controlled trial, will allocate hospitals in a 1:1 ratio to manage NSTEACS by standard care or according to the GRACE risk score and associated international guidelines. UKGRIS will recruit a minimum of 3000 patients from at least 30 English National Health Service hospitals and collect healthcare data from national electronic health records. The co-primary endpoints are the use of guideline-indicated therapies, and the composite of cardiovascular death, non-fatal myocardial infarction, new onset heart failure hospitalisation or cardiovascular readmission at 12 months. Secondary endpoints include duration of inpatient hospital stay over 12 months, EQ-5D-5L responses and utilities, unscheduled revascularisation and the components of the composite endpoint over 12 months follow-up.

**Ethics and dissemination:**

The study has ethical approval (North East - Tyne & Wear South Research Ethics Committee reference: 14/NE/1180). Findings will be announced at relevant conferences and published in peer-reviewed journals in line with the funder’s open access policy.

**Trial registration number:**

ISRCTN29731761; Pre-results.

Strengths and limitations of this studyUK GRACE Risk Score Intervention Study is a trial of patient management according to a risk model to reduce adverse patient clinical outcomes. This assessment of the effectiveness of risk stratification uses level one scientific methods.The design, intervention, patient population and outcomes are sufficiently similar to existing and planned international trials to facilitate individual participant data meta-analysis.The trial will use nationwide patient–level health records to enhance baseline and outcomes information derived from clinical records and patient questionnaires.Compliance with the assigned intervention at the cluster level requires monitoring, and clinical events cannot be centrally adjudicated, as they arise from electronic health records. As such, this is a pragmatic trial with results generalisable to the ‘real world’ clinical environment.

## Background

Non-ST-segment elevation acute coronary syndrome (NSTEACS) is a leading cause of disability, hospitalisation and death, and has major impacts on health economies.^1^ Since NSTEACS prognosis is determined by both baseline clinical risk and the use of evidence-based therapies, appropriately- stratified and effectively-delivered NSTEACS care has the potential to achieve cost-effective patient-centred treatment and improve clinical outcomes.^2–5^ For NSTEACS, however, there is a risk-treatment paradox whereby lower rather than higher risk patients are more likely to receive an invasive coronary strategy and more aggressive pharmacotherapies.^6–8^ The paradox is due to a number of factors including inaccurate and subjective risk assessment, under-recognition of the potential treatment benefits that higher risk cohorts may have, and cumulative missed care opportunities.^9–12^

Despite recommendation by national agencies such as the National Institute for Health and Care Excellence, the European Society of Cardiology and the American College of Cardiology (ACC)/American Heart Association (AHA),^2–5^ scoring systems which objectively characterise cardiovascular risk are not systematically applied to the management of NSTEACS.^12^ The Global Registry of Acute Coronary Events (GRACE) risk score tool is specifically designed for the risk stratification of patients with acute coronary syndrome (ACS), is aligned to treatment recommendations and, compared with other ACS risk scores, has superior discriminative performance.^13 14^ It was developed in an international registry programme to predict in-hospital and 6 month death or non-fatal myocardial infarction (MI) in a broad spectrum of ACS patients, and has since been derived and validated for these outcomes in over 42 000 patients with external validation in other cohorts.^15 16^ For clinical use, a simplified model was derived that predicts the risk of death alone, and the composite outcome of death or non-fatal MI, based on eight variables (age, heart rate, systolic blood pressure, Killip class, creatinine concentration, elevated biomarkers of myocardial injury, cardiac arrest on admission and ST-segment deviation). These factors conveyed more than 90% of the total risk and had a c-statistic of 0.81 for predicting death and 0.73 for predicting death or non-fatal MI from admission to 6 months after discharge.^17^ The GRACE risk score also shows good discriminatory performance for mortality at up to 2 years following discharge from hospital with ACS.^18^ The GRACE risk score has been updated (http://www.outcomes-umassmed.org/grace/) and shows good predictive accuracy of 1 year and 3 year mortality across a spectrum of ACS types.^19 20^

While evidence from registry data suggests that more comprehensive NSTEACS treatment is associated with improved outcome, there are no studies that have tested whether the prospective use of the GRACE risk score tool improves adherence to guideline recommendations for the management of NSTEACS and reduces adverse clinical outcomes.^8 21^ Complex behavioural interventions, such as the use of a risk score tool, have several interacting components. Typically, they present difficulties in (1) the standardisation of the design and delivery of the intervention, (2) their sensitivity to local context, (3) the organisational difficulty of applying experimental methods to service change and (4) the length and complexity of the causal chains linking the intervention with outcomes.^22^ It is not surprising, therefore, that some randomised controlled trials (RCTs) of complex interventions have failed to show improvements in outcomes, while others have succeeded.^23 24^

The UK is unique in that (1) national data are systematically and routinely collected for the populace regarding hospital healthcare utilisation and mortality, and for those admitted to hospitals with ACS information about cardiac investigations, pharmacotherapies and invasive coronary procedures^25^ and (2) the National Institute for Health Research through its Clinical Research Network supports National Health Service (NHS) hospitals to undertake research at scale. Thus, we aim to harness this national platform to undertake an efficient, pragmatic RCT to test the hypothesis that the use of the GRACE risk score tool will increase guideline-recommended treatment and decrease clinical events in NSTEACS patients.

## Methods and design

### Objectives

The UK GRACE Risk Score Intervention Study (UKGRIS; ISRCTN29731761, online supplementary file 1) will test the effectiveness of the use of the GRACE risk score tool by healthcare professionals on the delivery of guideline recommended care and clinical outcomes among patients hospitalised with NSTEACS. Co-primary objectives of the trial are:To determine whether implementing the GRACE risk score increases the use of class I guideline-indicated therapies for the management of NSTEACS within the guideline recommended time, compared with current standard care;To determine whether implementing the GRACE risk score reduces the composite endpoints of cardiovascular death, non-fatal MI, new onset heart failure and cardiovascular readmission at 12 months, compared with current standard care.

10.1136/bmjopen-2019-032165.supp1Supplementary data

Secondary objectives are to determine whether implementing the GRACE risk score has an impact on:Health-related quality of life at 12 months post-registration (measured by the EQ-5D-5L questionnaire);Occurrence of unscheduled coronary revascularisation within the 12 months of initial presentation;Duration of hospital stay within 12 months of initial presentation;The individual components of the co-primary composite endpoint within 12 months.

### Trial design

This publication describes V.3.0 of the UKGRIS protocol, dated 12^th^ November 2018.

UKGRIS is a two-arm 1:1 parallel-group, open-label, multicentre, cluster-randomised, controlled registry-based superiority trial. UK hospitals are eligible to participate in UKGRIS if they are acute NHS hospitals participating in the Myocardial Ischaemia National Audit Project and willing to implement the GRACE risk score tool if randomised to that arm. Hospitals are ineligible if they are already routinely using the GRACE risk score tool prior to randomisation.

#### Randomisation and blinding

Eligible hospitals (clusters) will be centrally randomised by the Leeds Clinical Trials Research Unit (CTRU) 1:1 to either GRACE risk score guided management or standard care using minimisation with a random element, aiming to ensure the cluster composition of each study arm is similar with respect to cluster-specific volume of patients hospitalised with ACS and primary percutaneous coronary intervention (PCI) capability. Site staff will not be blind to their assigned intervention, nor will recruited participants be blind to the intervention assigned to that site. Once a hospital has been randomised to the use of the GRACE risk score tool or to standard care, informed of their allocation and completed site initiation as required for their arm, a run-in phase will take place. During this time (up to 3 months for each site), the data collection and quality will be evaluated and the frequency of GRACE application in the intervention arm sites will be measured, as patients are recruited. (figure 1).

**Figure 1 F1:**
[figure not shown]
GRACE site recruitment and study run-in. CTRU, Leeds Clinical Trials Research Unit; GRACE, Global Registry of Acute Coronary Events.

### Eligibility criteria

Participants will be recruited from the randomised hospital to which they present. Eligibility criteria are deliberately broad and pragmatic: participants must be aged 18 years and above, hospitalised with NSTEACS (either non-ST-elevation myocardial infarction (NSTEMI) or unstable angina) and provide written informed consent (box 1). They must not present with ST-elevation myocardial infarction, or with NSTEACS precipitated by a clear non-cardiovascular cause (for example, motor vehicle accident, trauma, severe gastrointestinal bleeding, perioperative/periprocedural myocardial infarction) or be previously enrolled in the trial. Box 1Full eligibility criteria for participantsParticipant inclusion criteria1. Aged≥18 years2. Symptoms consistent with acute cardiac ischaemia for >10 mins within 24 hours of presentation to hospital plus either or both of:one of (a,b,c);at least two of the High Risk Features (d)(a) ECG changes:Transient ST-segment elevation of 0.5 mm in two or more contiguous leads;ST-segment depression of 0.5 mm in two or more contiguous leads;New T wave inversion of 1 mm in two or more contiguous leads;New Q waves (1/3 height of R wave or >0.04 s);New R wave>S wave in lead V1; or,New left bundle branch block(b) Elevated cardiac biomarkers:Troponin T or I above the upper reference limit (URL);
**creatine kinase**-muscle/brain (CK-MB) 2x URL; or,If there is no CK-MB available, then total CK greater than the local URL(c) Documented coronary artery disease:History of myocardial infarction (MI) or angina;Congestive cardiac failure due to ischaemia;Resuscitated sudden cardiac death;Prior or new positive stress test with or without imaging;Prior or new, cardiac catheterisation, percutaneous coronary artery intervention or coronary artery bypass graft surgery documenting coronary artery disease(d) **At least** two of the following High Risk features:Haemodynamic compromise (systolic blood pressure <90 mmHg and heart rate >100 bpm)Left ventricular systolic dysfunction (left ventricular ejection fraction <0.40);Presence of known diabetes mellitusDocumentation of chronic kidney disease (estimated glomerular filtration rate <60mls/min/m^2^)3. Willing and able to provide written informed consentParticipant exclusion criteriaPatients presenting at hospital due to an acute ST-segment elevation myocardial infarctionPatients presenting at hospital with an acute coronary syndrome accompanied with, or precipitate by significant comorbidity for example, motor vehicle accident, trauma, severe gastrointestinal bleedingPerioperative or periprocedural MIPatients already recruited into the studyPatients not living in the UK

The site Principal Investigator or a delegated member of the clinical research team will undertake the informed consent process. The participant will be approached within 12 hours of hospital admission (ideally in the emergency department or acute admission ward, whichever is closer to the time of hospitalisation), allowed time to consider the information and ask questions before deciding whether to participate. An optional oral consent pathway is available where participants will be provided with a shortened document describing the UKGRIS trial and after discussing the trial with the research nurse, can verbally consent to commence the care assigned to the admitting hospital. In hospitals allocated to GRACE, risk scores will be calculated and treatment recommendations made. Thereafter, the patient will be approached for full written informed consent. Participants who give oral consent at this point will be registered and complete the self-reported questionnaire and frailty score. Participants who give oral consent and refuse written informed consent will be excluded, and completed case record forms (CRFs) destroyed.

The informed consent process will request consent for data from all registeredpatients to be included in planned collaborative international analysis to investigate the GRACE risk score internationally, based on a planned individual patient data (IPD) meta-analysis of similar trials in Australia and Canada.^26^ The right of the participant to refuse participation without prejudice to future care will be respected, as will be the right to withdraw consent to further participation.

Efforts to ensure adequate and broad recruitment of all eligible patients in both arms through site research staff include: designation of a site ‘champion’, responsible for ensuring all staff are aware of the study and regular contacts to identify barriers to recruitment and/or trial compliance, trial posters, a twitter account (@UKGRIS_Trial).

### Trial status

The first site opened to recruitment on 13^th^ February, 2017, and the first patient was recruited on 13^th^ March, 2017. At the time of manuscript submission, 39 hospitals had been randomised to a study arm (of which 30 have registered at least one patient), and 2515 patients had consented to take part. Recruitment is expected to end on 31^st^ December, 2019, with end of follow-up ending on 31^st^ December, 2020, and completion of analysis by 30^th^ June, 2021.

### Interventions

#### GRACE risk score tool

Consenting participants recruited from hospitals in the intervention arm will receive care determined by staff trained to use the GRACE risk score tool and provided with a paper scoring table. Each consenting participant will have their risk score and corresponding 6 month mortality risk estimated by the appointed healthcare professional within 12 hours of hospitalisation. GRACE risk scores are categorised as ‘low’ (0 to 108), ‘intermediate’ (109 to 140) or ‘high’ (≥141), and the risk score nomogram (figure 2) will list recommended therapies (including pharmacological, invasive, non-invasive and behavioural interventions and tests) for patients based on their risk category (figure 3). At the same time as the GRACE risk score is calculated, sites will complete the CRUSADE bleeding risk score (Can Rapid risk stratification of Unstable angina patients Suppress ADverse outcomes with Early implementation of the ACC/AHA Guidelines).^27^ Both GRACE and CRUSADE will be completed using pen and paper scoring tables provided by the CTRU, online scoring applications and websites will not be used. Figure 2 illustrates the GRACE risk score nomogram as used in UKGRIS, while figure 3 illustrates the resulting recommendations arising from the scores obtained. Sites are invited to justify their decisions in declining to follow a recommendation on the grounds of contraindication. As part of the site initiation process, intervention sites will be informed as to how to complete the GRACE risk score paper nomogram, and follow its resulting recommendations. Sites will be monitored by telephone interviews with the ‘site champion’ throughout recruitment to ensure that GRACE and CRUSADE scoring is still routinely used for managing patients with NSTEACS. If GRACE sites stop routinely using the GRACE and CRUSADE risk scores, they will be asked to resume their use, and to cease recruitment to the UKGRIS trial if they fail to do so.

**Figure 2 F2:**
[figure not shown]
GRACE and CRUSADE risk scoring paper chart (completed by intervention sites only, and not distributed to control arm sites). CRUSADE, Can Rapid risk stratification of Unstable angina patients Suppress ADverse outcomes with Early implementation of the ACC/AHA Guidelines; CTRU, Leeds Clinical Trials Research Unit; eGFR, estimated glomerular filtration rate; GRACE, Global Registry of Acute Coronary Events; Hct, haematocrit; SBP, systolic blood pressure; UKGRIS, UK GRACE Risk Score Intervention Study.

**Figure 3 F3:**
[figure not shown]
Associated guideline recommended therapies for GRACE risk score categories (completed by intervention sites only, not distributed to control arm sites). ACE, angiotensin-converting enzyme; ARB, angiotensin receptor blocker; CTRU, Leeds Clinical Trials Research Unit; GRACE, Global Registry of Acute Coronary Events; LV, left ventricular; MI, myocardial infarction; NICE, National Institute for Health and Care Excellence; NSTEACS, non-ST-segment elevation acute coronary syndrome; PCI, percutaneous coronary intervention; STEMI, ST-elevation myocardial infarction; UA, urinalysis; UF, unfractionated; UKGRIS, UK GRACE Risk Score Intervention Study.

#### Standard care

Hospitals randomised to standard care will treat patients according to local practice (without using the GRACE risk score tool and associated clinical prompts) (figure 1). Sites will be monitored by telephone interviews with the ‘site champion’ throughout recruitment to ensure that processes for managing patients with NSTEACS are unchanged and that the management according to the GRACE risk score has not been systematically implemented due to a change in hospital policy. Standard care-assigned sites should not be routinely using the GRACE risk score nor the CRUSADE bleeding risk score to manage NSTEACS patients while taking part in the trial. Standard care sites implementing either scoring system during the study (as identified during regular site monitoring updates) will be asked to cease use and will stop recruitment to the UKGRIS trial if routine use continues.

### Outcome measures

There are two co-primary endpoints: (i) the uptake of class I guideline-indicated therapies (specifically, the 11 listed in online supplementary file 2) and (ii) the composite of cardiovascular death, non-fatal myocardial infarction, hospitalisation for new onset heart failure or cardiovascular readmission, at 12 months (table 1, with subsequently derived outcome measures in table 2). Secondary endpoints are total duration of inpatient stay, quality of life based on EQ-5D-5L^28^ responses and utilities, unscheduled coronary revascularisation and the components of the composite endpoint over 12 months follow-up.

10.1136/bmjopen-2019-032165.supp2Supplementary data

**Table 1 T1:** Schematic of assessments

TIME POINT*	Cluster identification	Cluster allocation	Patient identification	Patient registration	Post-allocation		
	*-t_3_*	*-t_2_*	-t_1_	*0*	*t_A_*	*t_D_*	***12*** m
CLUSTER ENROLMENT:							
Eligibility screen	X						
Essential documents	X						
Randomisation		X					
Site initiation		X					
PATIENT ENROLMENT:							
Eligibility			X				
Informed consent			X				
Registration				X			
INTERVENTIONS:							
GRACE/CRUSADE risk scoring (X) and subsequent care					X		
Standard care					X		
ASSESSMENTS:							
Baseline assessments*				X			
EQ-5D-5L				X			X
Edmonton frailty score				X			
Numbers of class I guideline indicated therapies					X		
Numbers of therapies received						X	X
Date of discharge						X	
Final diagnosis						X	
Medications prescribed acutely during hospital stay or on discharge						X	
In-hospital cardiovascular procedures						X	
In-hospital outcomes						X	
Other cardiac investigations and treatments						X	
Health advice given						X	
Hospitalisations							X
Deaths							X
Unscheduled revascularisations							X

*Time points: -t_3_, -t_2_, -t_1_ are three arbitrary time points that occur at any time (but in the given order) prior to individual patient enrolment at time 0. Post registration, t_A_ and t_D_ are the time points at which a participant is assessed according to the cluster-randomised strategy and discharged from hospital. Subsequent follow-up is at 12 months.

†Baseline assessments are: age, sex, ethnicity, height, weight, date and time of symptoms onset and admission to hospital, ECG ST-segment deviation, heart rate on admission, systolic blood pressure on admission, Killip class, diuretic usage, creatinine, troponin (date, time and elevated), cardiac arrest occurrence, haematocrit, peripheral vascular disease, diabetes mellitus, congestive cardiac failure.

CRUSADE, Can Rapid risk stratification of Unstable angina patients Suppress ADverse outcomes with Early implementation of the ACC/AHA Guidelines; GRACE, Global Registry of Acute Coronary Events.

**Table 2 T2:** Definitions of UKGRIS outcome measures and primary analyses

Outcome measure	Assessed at	Analysis method
**Co-primary**		
(1) Number of class I guideline indicated processes received per patient (see online supplementary file 2 for full description)	Discharge	Logistic regression, modelling agreement between eligibility and receipt of process as function of treatment arm, including fixed effects for minimisation factors, random hospital effect and random patient effect.
(2) Time from registration until first occurrence of one of the following * cardiac death, * new onset heart failure, * non-fatal MI, or * cardiovascular hospitalisation	12 months post registration	Kaplan-Meier survival estimates; appropriate time-to-event regression (eg, proportional hazards, flexible parametric model^47^) including fixed effects for minimisation factors and random hospital effect, (sensitivity analysis: also accounts for competing risks of non-cardiac death and withdrawal from follow-up.)

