### Statistical methods

#### Sample size

A minimum of 30 clusters, each recruiting 100 participants (ie, 3000 in total) will give 80% power to detect clinically relevant differences in the co-primary endpoints with two-sided 5% significance tests (see sections 7.2.1 and 7.2.3 of^34^). For the proportion of class I guideline-recommended therapies implemented, this assumes 95%^35^ of recommended therapies implemented in the control arm and will detect an absolute increase of 3% to 98% in the GRACE arm, with an assumed coefficient of variation (CV) in cluster outcomes of 0.02. For time to first cardiac outcome, a fixed recruitment of 15 clusters of 100 patients per arm gives 80% power to detect a difference in 12 month rates of 13% and 10.4% between standard care and GRACE arms, assuming a mean follow-up of 27 months and CV of cluster event rates of 0.05. Both endpoints require 14 clusters of 100 patients in each arm to have 80% power, though no adjustment for multiple testing was made. Recruiting 15 clusters per arm allows for attrition of 7% to 10%. For more details, see online supplementary file 3. Additional sites have been and will be opened to ensure that target recruitment is achieved, and to safeguard study power should these assumptions not be met.

10.1136/bmjopen-2019-032165.supp3Supplementary data

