UKGRIS will collect clinical data from a range of national EHRs. Limitations inherent in this approach include non-capture of all data relating to the disease (data missing by design), missing and corrupt data as recorded in routine national databases, time lag of data acquisition, non-consent for data capture, contamination and lack of fidelity. UKGRIS aims to be a streamlined and pragmatical registry-based trial, answering finite questions efficiently. As such, *a priori* endpoints were designed around the availability of data (for example, hospitalised rather than all new heart failure diagnoses), and key safety outcomes (mortality) will be requested from the UK Office for National Statistics. Missing and corrupt data are infrequent in national administrative database and for clinical registries we will augment data collection through the CRFs. We assume data anomalies will be equally balanced between intervention and control arms through randomisation. To reduce the potential for within-site contamination of the intervention, UKGRIS will randomise to the intervention at the hospital level, and treatment arm fidelity will be monitored and maintained by regular contact with each site. We should acknowledge that clinicians at all sites may improve their individual guideline implementation rates due to the Hawthorne effect of taking part in the study. Existing registry data for patients not taking part may indicate how GRACE trial performance differs from ‘real-world’ practice.

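### The guideline-uptake model leaves unused each hospital's pre-randomisation uptake, which the national audit could partly supply; this costs precision and leaves the result open to chance imbalance, but is not bias

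*Protocol article*

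**What the plan says.** Table 2 of the protocol article sets the analysis of co-primary (1): logistic regression of agreement between eligibility and receipt on treatment arm, with "fixed effects for minimisation factors, random hospital effect" and a random patient effect. Under Randomisation and blinding, minimisation aims to make the arms "similar with respect to cluster-specific volume of patients hospitalised with ACS and primary percutaneous coronary intervention (PCI) capability". Prior guideline uptake therefore enters neither the allocation nor the model.

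Under Trial design, eligible hospitals are "acute NHS hospitals participating in the Myocardial Ischaemia National Audit Project". The Background says that national data routinely cover cardiac investigations, drug treatment and invasive procedures for ACS admissions. Data collection already draws on the national cardiovascular registries for follow-up. The Discussion considers registry data beyond the participants, but for another purpose: "Existing registry data for patients not taking part may indicate how GRACE trial performance differs" from everyday practice.

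The same table adjusts the secondary EQ-5D-5L utility analysis for its baseline value.

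Sample size states "A minimum of 30 clusters, each recruiting 100 participants (ie, 3000 in total) will give 80% power" "with two-sided 5% significance tests". For uptake it takes 95% against 98%, "an assumed coefficient of variation (CV) in cluster outcomes of 0.02", and 14 clusters of 100 needed per arm.

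**The concern.** Uptake is a product of hospital practice, so a hospital's own past uptake may be the strongest available predictor of its uptake in the trial. Volume and PCI capability are indirect substitutes for it. With about 15 hospitals per arm, randomisation can leave the arms noticeably different in prior practice, and the planned model can use only those two factors to explain the difference. The unexplained part stays in the random hospital effect and widens the confidence interval.

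Two things are at stake. One is power for co-primary (1), where hospital variation is a large share of the variance. The other is how convincing the single realised allocation will be. If prior practice is not tabulated, readers cannot tell whether a difference of a point or two was there before the trial. If it is tabulated and adjusted for only after the results are known, the choice is open to dispute.

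**Working it through.** **Inputs** (Sample size section unless stated): control uptake p0 = 0.95; target p1 = 0.98; m = 100 patients per hospital; CV k = 0.02; two-sided 5%; 80% power; 15 hospitals per arm. The correlation r between a hospital's prior and trial uptake is not in the document, so it is assumed and a range is shown.

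**1. The plan's own figure.** Unmatched cluster formula for proportions:

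c = 1 + (1.96 + 0.84)² × [p0(1−p0)/m + p1(1−p1)/m + k²(p0² + p1²)] / (p1−p0)²

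- Patient part: A = 0.0475/100 + 0.0196/100 = 0.000671
- Hospital part: B = 0.0004 × (0.9025 + 0.9604) = 0.000745
- c = 1 + 7.849 × 0.001416 / 0.0009 = 13.35, rounded up to 14. The stated figure is reproduced.

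**2. Hospital share of the variance.** 0.000745 / 0.001416 = 53%.

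**3. Chance arm difference from hospitals alone, 15 against 15.**

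- Hospital SD = 0.02 × 0.95 = 1.9 points
- SE = 1.9 × √(2/15) = 0.69 points, 23% of the 3-point target
- Mean absolute difference = 0.69 × √(2/π) = 0.55 points, 18% of the target
- 95% limit = 1.96 × 0.69 = 1.36 points, 45% of the target

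With CV 0.01 or 0.03 in place of 0.02, the 95% limit is 23% or 68% of the target. If all 39 hospitals randomised at submission contributed (19.5 per arm on average), it would be 1.19 points (40%).

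**4. Power with the covariate.** The hospital part is multiplied by (1−r²), and c−1 = 14 is used as in the plan's formula:

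Power = Φ(√[14 × 0.0009 / (A + B(1−r²))] − 1.96)

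| r (assumed) | Power, 15 per arm |
|---|---|
| 0 | 84.7% |
| 0.3 | 86.3% |
| 0.5 | 89.3% |
| 0.7 | 93.4% |
| 0.8 | 95.6% |

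The hospitals needed per arm for 80% power fall from 14 to 12, 11 or 10 at r = 0.5, 0.7 or 0.8.

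**5. Error rate.** In 40,000 simulated null trials (15 against 15, CV 0.02, unadjusted cluster-level t-test), type I error was 5.1% overall. Among the roughly 5% of allocations with a true hospital imbalance above 1.36 points, it was 29%. The test is valid over all allocations; an unlucky one is where adjustment would matter most.

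**The case against.** A reader might infer from the 45% figure that prior practice is an uncontrolled confounder able to produce nearly half the target effect, or that the planned test rejects too often. The document does not support either reading. Allocation is random, the random hospital effect puts between-hospital variation into the standard error, the sample size includes it through the CV, and overall type I error stays near 5%. The 45% is a 95% limit, exceeded in either direction in about one allocation in twenty. It is also an upper bound, because it treats all hospital variation as stable practice unrelated to volume and PCI capability, both of which are in the model.

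Other objections stand in part:

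- The gain depends on an unknown correlation. At r = 0.3 it is under two percentage points of power, and unadjusted power already exceeds 80%.
- The audit figure is an imperfect proxy. The document does not show that the audit holds all 11 processes or the same eligibility denominator, and it would describe non-trial patients. The Discussion itself expects behaviour inside the trial to differ from usual practice.
- The linkage described under Data collection is for consenting patients, so an aggregate figure on earlier admissions is a separate request.
- The power figures come from a risk-difference formula, not from the planned logistic model with two random effects.
- The analysis plan, which is not shown, may add covariates.

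These points reduce the expected gain but do not remove it. Table 2 states a specific model, and a value fixed before randomisation cannot be affected by allocation.

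**Conclusion.** The point holds as a worthwhile, low-cost improvement to precision. The planned analysis is valid. What it gives up, on the plan's own inputs, is the chance to explain part of a hospital component that makes up 53% of the variance. A typical chance difference is about 0.55 to 0.7 points, and the 95% limit is about 1.4 points.

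The benefit at 15 hospitals of 100 per arm runs from none at r = 0 to about 11 percentage points of power at r = 0.8. It rests on the CV of 0.02, on an assumed r, and on the risk-difference approximation carrying over to the logistic model. If the CV were 0.03 (an assumption), the same formula gives about 64% power unadjusted and about 82% with r = 0.7, so the covariate also gives some protection if hospitals vary more than planned.

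**What to change.** Before any comparative analysis, request from the audit one aggregate figure per hospital: uptake of those listed therapies that the audit records, in NSTEACS admissions during the 12 months before that hospital's randomisation. Prespecify it as a hospital-level fixed covariate in the co-primary (1) model, or at the least in a prespecified sensitivity analysis. Show it by arm in the hospital baseline table, for all randomised hospitals and for those that registered patients (39 and 30 at submission).

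The cost is one aggregate registry request, a line in the analysis plan, and one of roughly 28 hospital-level degrees of freedom. State which of the 11 processes the figure covers and that it describes non-trial patients, so that its limits as a proxy are clear.
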